## Abstract

**Background:**

Exercise training is effective in improving functional capacity and quality of life in patients with coronary artery disease, but its effects on left ventricular systolic and diastolic function are controversial. Diastolic dysfunction is a major determinant of adverse outcome after myocardial infarction and, contrary to systolic function, no therapy or intervention has proved to significantly improve diastolic function. Data from animal studies and from patients with diastolic heart failure has suggested that exercise training can have a positive effect on diastolic function parameters.

This trial aims to evaluate if a structured exercise training program can improve resting left ventricular diastolic and systolic function in patients who have had an acute myocardial infarction.

**Methods/Design:**

This is a phase II, prospective, randomized, open-label, blinded-endpoint trial that will include at least 96 consecutive patients who have had an acute myocardial infarction one month previously. Patients will be randomized (1:1) to an exercise training program or a control group, receiving standard of care. At enrolment, and at the end of the follow-up period, patients will be submitted to an echocardiography (with detailed assessment of diastolic and systolic function using recent consensus guidelines), cardiopulmonary exercise testing, an anthropometric assessment, blood testing, and clinical evaluation. Patients randomized to the intervention group will be submitted to an eight-week outpatient exercise program, combining endurance and resistance training, for three sessions per week. The primary endpoint will be the change in lateral E’ velocity immediately after the eight-week exercise training program. Secondary endpoints will include other echocardiographic parameters of left ventricular diastolic and systolic function, cardiac structure, metabolic and inflammation biomarkers (high-sensitivity C-reactive protein and pro-BNP), functional capacity (peak oxygen consumption and anaerobic threshold) and anthropometric measurements.

**Discussion:**

New strategies that can improve left ventricular diastolic function are clinically needed. This will be the first trial to evaluate, in patients who have had an acute myocardial infarction, the effects of a structured program of exercise training on diastolic and systolic function, assessed by novel echocardiographic parameters.

**Trial registration:**

Registered with ClinicalTrials.gov (reference: NCT02224495) on 21 August 2014.

## Background

Exercise training is effective in improving functional capacity and quality of life in patients with coronary artery disease [1,2]. It is known that exercise can improve several cardiovascular and non-cardiovascular parameters, such as glucose metabolism, skeletal muscle function, oxidative stress, vascular function, pulmonary circulation, ischemia-reperfusion lesion, and ventricular remodelling [3].

However, the effect of exercise training on left ventricle systolic and diastolic function is still controversial [4-6], especially after acute myocardial infarction (AMI), where no longitudinal study has evaluated cardiac function using modern echocardiographic parameters, such as those derived from tissue Doppler analysis. After AMI, the effect of exercise training on diastolic function can be clinically relevant because the majority of these patients have diastolic dysfunction (DD) [4,7,8] and, most importantly, because no therapy or intervention has been shown to significantly improve diastolic function [9]. Data from animal studies are encouraging, showing that endurance training can improve myocardial relaxation and calcium homeostasis by increasing the myocardial expression of *SERCA2a* and phospholamban (*PLB*) [10,11]. Also, a recent study evaluating patients with heart failure with preserved ejection fraction (also known as diastolic heart failure) has shown that the combination of endurance and resistance training can improve diastolic function parameters [12]. Finally, it is also still controversial whether systolic function can be improved by exercise training [4,13,14]. Most of these studies were small, lacked control groups, and evaluated systolic function only by ejection fraction, which has several limitations in the evaluation of global left ventricle systolic function [15].

In this trial our aim is to assess, in patients who have had an AMI, if a structured exercise training program can improve resting left ventricular systolic and diastolic function.

## Methods/Design

### Trial design

In this prospective, randomized, open-label, blinded-endpoint (**“The Effect of Exercise Training on Cardiac Structure and Function”**) trial, patients who have had an AMI one month previously will be randomized (1:1) to be included in an eight-week duration exercise training program or a control group, receiving standard of care. Immediately before enrolment and at the end of the follow-up period, patients will be submitted to a clinical evaluation, detailed echocardiography, cardiopulmonary exercise testing, and an anthropometric assessment, according to the study design outlined in Figure 1. Because the intervention is a structured exercise training program, it is not possible to perform patient blinding. However, the medical staff performing all the measurements will be blinded to the type of intervention.

**Figure 1 Fig1:**
[figure not shown]
**Design of the trial.** In this prospective, randomized, open-label, blinded-endpoint trial consecutive patients who have had an acute myocardial infarction one month previously will be randomized (1:1) to an eight-week outpatient exercise training program or standard of care. The primary endpoint will be the change in lateral E’ velocity between baseline and follow-up.

Randomization by blocks will be used with an allocation sequence based on a fixed block size of eight, generated with a computer random number generator.

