### Participants

Eligible patients will be consecutive individuals admitted to Gaia Hospital Centre (a tertiary care hospital with a reference population of 700,000 patients) after AMI, including both ST-elevation and non-ST elevation myocardial infarction. For inclusion in the study, we will use the criteria in the universal definition of myocardial infarction [16]. Table 1 details the study’s inclusion and exclusion criteria.

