**Table 1 Tab1:** **Study population: inclusion and exclusion criteria**

**Inclusion criteria:**	
Between 18 and 75-years-old	
Acute myocardial infarction (according to the universal definition of myocardial infarction [16])	
Both ST elevation and non-ST elevation myocardial infarction	
One month since discharge	
Left ventricular ejection fraction >30%	
Able to exercise	

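### A single fixed block size of eight in an open-label trial at one named hospital would let a recruiter who knew the block size and tracked both arms foresee one allocation in five, so selection bias is possible

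*Protocol article*

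**What the plan says.** The text below Figure 1 in the protocol article gives the method: "Randomization by blocks will be used with an allocation sequence based on a fixed block size of eight", the sequence being "generated with a computer random number generator". The Figure 1 legend gives the ratio: patients "will be randomized (1:1) to an eight-week outpatient exercise training program or standard of care".

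Three other statements bear on this:

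- **Blinding.** Under Trial design, "it is not possible to perform patient blinding", while "the medical staff performing all the measurements will be blinded to the type of intervention". Nothing is said about the staff who recruit.
- **Setting.** Under Participants, "Eligible patients will be consecutive individuals admitted to Gaia Hospital Centre". No other hospital is named.
- **Eligibility.** Table 1 includes "Able to exercise" with no measurable threshold. Beside it stand objective limits on ejection fraction, spirometry, creatinine clearance and haemoglobin.

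Trial status reports recruitment finished, with 188 patients included.

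**The concern.** Blocks of constant size return to exact balance at known points. Once four patients in a block have gone to one arm, every remaining place in that block belongs to the other arm. In an open-label trial past allocations can become known to those who enrol. Hiding the list does not then prevent inference about the next entry.

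If the person judging eligibility expects exercise next, a borderline patient may be judged differently than if control is expected. The arms could then differ in prognosis before treatment starts. A blinded echocardiographer would measure that difference faithfully and could not remove it. The covariates in the primary model (baseline E', age, mean arterial pressure, gender, baseline diastolic dysfunction grade) would remove only the part they capture. Peak VO2, a direct measure of fitness, is not among them.

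**Working it through.** **The plan's own figure.** The article gives no predictability figure. Its sample size reproduces and is not affected: n per group = 2 × (1.960 + 1.282)² × 1.5² / 1² = 47.3, rounded up to 48 (two-sided 5% assumed, 90% power).

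**Inputs.** Block size 8 and ratio 1:1, so m = 4 per arm per block (Figure 1). Planned total 96 = 12 complete blocks. Included 188 = 23 complete blocks plus 4 patients (Trial status).

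**Allocations known with certainty.** There are C(8,4) = 70 equally likely blocks. The forced allocations are the final run of identical assignments.

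| Forced at block end | Blocks of 70 | Probability |
|---|---|---|
| 1 | 40 | 0.571 |
| 2 | 20 | 0.286 |
| 3 | 8 | 0.114 |
| 4 | 2 | 0.029 |

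Mean = (40×1 + 20×2 + 8×3 + 2×4)/70 = 112/70 = 1.6. The closed form 2m/(m+1) = 8/5 agrees. The share is 1.6/8 = 20.0%.

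- Planned 96: 12 × 1.6 = 19.2.
- Included 188: 23 × 1.6 = 36.8 (19.6%). The four patients in the incomplete block add none, because an allocation can be forced only from the fifth place on.

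**Better-than-chance guessing.** Guess the arm that is behind, and toss a coin when level. Expected correct per block = m + 2^(2m−1)/C(2m,m) − 1/2 = 4 + 128/70 − 0.5 = 5.33, or 66.6%. Certainty requires the block size, the block starts and the allocations in both arms. This weaker guess needs only the running totals of both arms, because they are level at every block end.

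**Alternatives.** The certainty shares for varying sizes come from simulating 188 patients, with a recruiter who knows the set of sizes and every earlier allocation. The sets are illustrative assumptions.

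| Scheme | Known with certainty | Lagging-arm guess correct |
|---|---|---|
| Fixed 6 | 25.0% | 68.3% |
| Fixed 8 (plan) | 20.0% | 66.6% |
| Fixed 10 | 16.7% | 65.3% |
| Random from 4, 8 | about 7.8% | about 68% |
| Random from 4, 6, 8 | about 2.3% | about 68% |

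For sizes 4, 6 and 8 the guess rate is the length-weighted mean (4×0.708 + 6×0.683 + 8×0.666)/18 = 0.681. Varying the size therefore removes most of the certainty but not the advantage of guessing the lagging arm.

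**The case against.** The best defence is that foresight has conditions the article does not show were met. It does not say who enrolled, who held the list or who knew the block size. Concealment procedures are commonly left to the full protocol, so their absence here is no fault. The article reports recruitment finished, so it did not itself disclose the block size while patients were entering. Patients were to be consecutive and enrolled one month after discharge, most eligibility limits are objective, and baseline testing comes before enrolment. All of this stands and lowers the risk. It does not remove it, because ability to exercise is judged patient by patient.

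Four stronger readings are tempting but unsupported:

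- **Counting programme entrants reveals the balance.** It reveals one arm only. The number allocated to control is needed too, and those patients receive standard of care.
- **Staff could choose when to enrol.** Nothing says so; consecutive enrolment at a set time points the other way.
- **There was certainly no stratification.** The article is silent. If there were strata, the 20% would apply to complete blocks within each stratum, and the count for 188 would change.
- **The bias has a known size.** If recruiters shifted the expected change in E' by 0.1 to 0.3 SD on every guess (an assumption), the false difference would be 2 × 0.332 × 0.15 to 0.45 cm/s = 0.10 to 0.30 cm/s, against a target of 1 cm/s. Here 0.332 is the excess of right over wrong guesses (0.666 − 0.334). The shift has no source in the article, steering at every place conflicts with consecutive enrolment, and the figure precedes covariate adjustment.

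**Conclusion.** The concern holds as a conditional design weakness that should be addressed. The fixed block of eight is stated, and its predictability is exact arithmetic: 20% of allocations certain (19.2 of 96; about 36.8 of 188) and 66.6% guessed correctly within complete blocks. The certainty figure assumes a recruiter who knew the block size and followed both arms; the guess rate assumes knowledge of both arms' running totals. The 188-patient count also assumes a single unstratified sequence.

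A reader might infer that the randomisation was compromised or the primary result is biased. The article supports neither. It shows that selection was possible, not that it happened, and it supplies no basis for a bias in cm/s.

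**What to change.** **Design stage (this trial's successor).** Use randomly varying block sizes, for example drawn from 4, 6 and 8, and disclose neither the sizes nor the list to anyone who enrols, trains or measures patients. Certain allocations fall from 20% to about 2%, and 48 per group is unchanged. The cost is a slightly larger possible imbalance at the end: with a largest block of 8, at most 4 patients (50 against 46 at 96), where twelve complete blocks of eight give none. Non-disclosure still matters, because varying sizes do not lower the lagging-arm guess rate.

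**Now that recruitment has finished.** Pre-specify a check from the existing allocation list:

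1. For each patient in order of entry, compute the probability that exercise was next: exercise places left in the block divided by all places left.
2. Compare baseline E', peak VO2 and age across that probability. Without selection they should be unrelated to it.
3. Keep the intention-to-treat analysis as primary. Add one sensitivity analysis that adjusts for this probability or omits the fully determined allocations. Adjustment is the more informative choice: omission would drop about 37 of 188 patients and leave the non-forced guesses in place.

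The cost is one extra analysis of data already held.

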### Participants

Eligible patients will be consecutive individuals admitted to Gaia Hospital Centre (a tertiary care hospital with a reference population of 700,000 patients) after AMI, including both ST-elevation and non-ST elevation myocardial infarction. For inclusion in the study, we will use the criteria in the universal definition of myocardial infarction [16]. Table 1 details the study’s inclusion and exclusion criteria.

**Table 1 Tab1:** **Study population: inclusion and exclusion criteria**

**Inclusion criteria:**	
Between 18 and 75-years-old	
Acute myocardial infarction (according to the universal definition of myocardial infarction [16])	
Both ST elevation and non-ST elevation myocardial infarction	
One month since discharge	
Left ventricular ejection fraction >30%	
Able to exercise	
**Exclusion criteria**	
Moderate or severe valvular disease	
Atrial fibrillation	
Uncontrolled atrial or ventricular tachyarrhythmias	
Exercise-induced myocardial ischemia	
Pericardial disease	
Moderate or severe chronic lung disease (vital capacity and/or forced expiratory volume in 1 second <80% of age-dependent predicted value)	
Severe renal disease or dysfunction (creatinine clearance <30 mL/min, calculated by the Cockcroft-Gault formula)	
Anaemia (hemoglobin <12 g/dL)	

### Intervention: the exercise training program

Patients randomized to the exercise training group will be included in an eight-week outpatient program, encompassing three sessions per week, combining endurance and resistance training. Each session will consist of 10 minutes of warm up, 50 minutes of aerobic and resistance training, and 10 minutes of cool down. During the eight weeks, endurance training (cycling in the first four weeks and treadmill in the remaining four weeks) of increasing intensity will be performed. Training intensity will be individualized to a target heart rate of 70 to 85% of the maximal heart rate achieved in the baseline cardiopulmonary exercise test. Resistance training will also be included in each session consisting of arm, leg, and thoracic exercises, including dumbbell or weight training depending, on the patient’s condition and exercise capacity. Clinical and training parameters will be monitored throughout the exercise including arterial blood pressure, heart rate, glycaemia (in diabetic patients), and training level intensity. Fatigue will be monitored using the Borg scale.

Patients randomized to the control group will receive standard of care, with regular appointments with the cardiologist, optimized medication, and recommendations on healthy lifestyle.

### Measurements: the echocardiographic evaluation protocol

A single experienced cardiologist, blinded to the patient assignment group, will perform all echocardiographic studies using an ultrasound system (iE33, Philips Medical Solutions, Best, The Netherlands) equipped with an S5-1 and X5-1 transducer. Cardiac chamber dimensions, volumes, and left ventricular mass will be measured according to current recommendations and indexed to body surface area [17]. Mitral inflow velocities will be accessed using pulsed-wave Doppler in the apical four-chamber view, placed between the tips of the mitral leaflets and velocities recorded at end-expiration. Tissue Doppler velocities will also be acquired at end-expiration, in the apical four-chamber view, with the sample positioned at the septal and lateral mitral annulus for determination of systolic (S’), early diastolic (E’), and late diastolic (A’) velocities. Pulsed wave Doppler velocities at the upper right pulmonary vein will also be recorded to calculate the Ard-Ad relation: the time difference between the duration of the atrial reverse wave of the pulmonary flow (Ard) and the mitral A-wave duration. For all parameters, the average of three consecutive heart beats will be recorded.

Left ventricle diastolic function will be evaluated according to the EAE/ASE consensus guidelines on diastolic function evaluation [18], which include the determination of peak early (E) and late (A) diastolic mitral inflow velocities, deceleration time of early left ventricular filling (DT), E/A ratio, isovolumetric relaxation time (IVRT), myocardial early diastolic velocities at the septal and lateral side of mitral annulus (E’ septal, E’ lateral, and E’ mean), E/E’ ratio (including septal, lateral, and mean E/E’) and Ard-Ad relation. Moreover, using the consensus criteria [18], patients will be categorized in DD grades: normal diastolic function, grade I (mild DD), grade II (moderate DD), and grade III (severe DD), by two blinded independent cardiologists. In case of discordance, each case will be discussed individually.

Left ventricle systolic function will be evaluated by calculation of biplane ejection fraction (Simpson’s rule) and determination of systolic velocities at the septal and lateral side of mitral annulus by tissue Doppler (S’ septal and S’ lateral). It is known that, compared to ejection fraction, S’ velocities are more sensitive parameters for global and regional systolic function evaluation after myocardial infarction [19].

### Measurements: cardiopulmonary exercise testing

At the beginning and end of the study protocol, patients will be submitted to symptom-limited cardiopulmonary exercise testing on a treadmill, using the modified Bruce protocol (Cardiovit CS-200 Ergo Spiro; Schiller, Baar, Switzerland). Expired gases will be continuously collected throughout exercise and analyzed for ventilatory volume (VE) and for oxygen (O_2_) and carbon dioxide (CO_2_) content, using dedicated analyzers. Standard spirometry (forced expiratory volume in one second (FEV1) and forced vital capacity (FVC)) will also be performed before the exercise test. Equipment calibration and all measurements will be done according to the recommendations of the American Thoracic Society and American College of Chest Physicians [20]. The following variables will be calculated: peak oxygen consumption (pVO_2_), measured in milliliter per kilogram per minute (mL/Kg/min); peak respiratory exchange ratio, defined by the ratio of CO_2_ production to O_2_ consumption at peak effort; oxygen consumption at anaerobic threshold (AT), defined as the point at which CO_2_ production increases disproportionately in relation to O_2_ consumption, obtained from a graph plotting O_2_ consumption against CO_2_ production; and total exercise duration (seconds). It is known that cardiopulmonary exercise testing with O_2_ consumption measurement provides the most accurate, reliable, and reproducible measurements of exercise capacity [21]. We will assess exercise capacity mainly by measuring pVO_2_, which is considered the gold standard parameter for functional capacity assessment [22]. However, we will also evaluate submaximal exercise capacity by determination of the ventilatory AT that has the advantage of being relatively effort independent [21].

### Measurements: clinical, analytical, and anthropometric data

At baseline and at the end of the study protocol all patients will be submitted to a clinical evaluation performed by a cardiologist, a blood sample, and detailed anthropometric evaluation. The clinical evaluation will include an interview, review of medical registries, and a physical examination to collect data on cardiovascular risk factors, previous medical history, medication use or change since last evaluation, symptoms of angina, and New York Heart Association functional status (NYHA class).

The anthropometric evaluation will include the measurement of height, weight, waist circumference, and hip circumference. Body mass index ((BMI) weight/height^2^ in kg/m^2^) will be calculated for each subject. Waist circumference will be measured at the midpoint between the iliac crest and the lower rib margins, measured in the midaxillary line. Body composition will be assessed by bioelectrical impedance analysis (Tanita Inner Scan BC-522; Tanita, Tokyo, Japan) to determine body fat percentage (%).

A fasting venous blood sample will be obtained immediately before and after the study for measurement of glucose, total cholesterol, LDL-cholesterol, HDL-cholesterol, triglycerides, high-sensitivity C-reactive protein, and N-terminal pro-BNP. Insulin resistance will be assessed using the Homeostasis Model Assessment of Insulin Resistance (HOMA-IR) score.

### Study endpoints

The primary endpoint will be the change in E’ lateral velocity after the eight-week exercise training program. Secondary endpoints will be other echocardiographic parameters of left ventricular diastolic and systolic function, metabolic and inflammation biomarkers, functional capacity, and anthropometric measurements, as detailed in Study primary and secondary endpoints:**Primary endpoint**E’ lateral velocity: change between baseline and follow-up**Secondary endpoints**– Left ventricular diastolic function parameters:E’ septal velocity; E/E’ septal, lateral and mean ratio; E/A ratio; E-wave deceleration time; isovolumetric relaxation time; diastolic dysfunction grades according to the ASE/ESE consensus– Systolic function parameters:Ejection fraction, S’ lateral and septal velocities– Functional capacity parameters:Peak VO_2_; VO_2_ at anaerobic threshold; exercise duration– Metabolic biomarkers:Insulin and glucose plasma levels; insulin resistance (Homeostasis Model Assessment);– Cardiovascular biomarkers:N-terminal pro-BNP and high sensitivity C-reactive protein– Anthropometric parameters:Weight, body mass index, waist and hip perimeter, fat mass percentage by bioimpedance analysis

